### Title:

A multi-center, individual-level randomized, 18-month, parallel-group superiority trial to compare the efficacy of a complex primary care practice network-based care management intervention versus usual care in the improvement of self-care behavior among patients with type II diabetes and multiple comorbidities (GEDIMApplus)

## List of Acronyms

|         |                                                                                           |
|---------|-------------------------------------------------------------------------------------------|
| AMV     | Dept. Of General Practice and Health Services Research,
University Hospital Heidelberg |
| BMBF    | Federal Ministry of Education and Research                                                |
| DA      | Dialogue assistant                                                                        |
| FUPHV   | Follow-up home visit                                                                      |
| GGM     | Genossenschaft Gesundheitsprojekt Mannheim e.G.                                           |
| HCA     | Health care assistant                                                                     |
| HRQL    | Health related quality of life                                                            |
| IQWiG   | Institute for Quality and Efficiency in Health Care                                       |
| IT      | Information Technology                                                                    |
| NCM     | Net-case manager                                                                          |
| PCP     | Primary care practice                                                                     |
| PCPnet  | Primary care practice-net                                                                 |
| PROs    | Patient reported outcomes                                                                 |
| PTC     | Pathway to change                                                                         |
| QALY    | Quality Adjusted Life-Years                                                               |
| SDSCA   | Summary of diabetes self-care activities measure                                          |
| SDSCA-G | Summary of diabetes self-care activities measure, German
version                       |
| SMBG    | Self-monitoring of blood glucose                                                          |
| TAU     | Treatment as Usual                                                                        |

## Summary

### Background:

The increasing prevalence of multiple, co-occurring chronic conditions places a burden for contemporary health systems. Care management interventions in the German healthcare system have been evaluated with promising results. However, further studies are necessary to explore the full potential of care management interventions for the improvement of outpatient diabetes care in the context of multi-morbidity in Germany.

### Objective:

To assess the efficacy of a primary care practice net-based, IT-supported care management intervention with integrated telephone monitoring for patients with diabetes type II and multiple co-occurring chronic conditions.

### Analysis:

The confirmatory, primary analysis will be performed following the intention-to-treat (ITT) principle. The efficacy of the intervention will be quantified using two-level linear regression stratified by type of medical treatment (insulin vs. non-insulin therapy). The effect of the intervention on the primary outcome will be adjusted for baseline values in SDSCA-G. Secondary analyses (related to the secondary objectives) will be performed according to ITT principle as well, followed by a complete case analysis as sensitivity analysis to assess the robustness of effect estimates. To relate cost differential to outcome differential between intervention and control group the incremental cost effectiveness ratio will be calculated. We will apply bootstrap methods to model uncertainties in costs. Maximum willingness to pay thresholds and cost-acceptability curves will be determined. Sensitivity analyses will provide information on robustness of assumptions.

## 1. Introduction

The increasing prevalence of multiple, co-occurring chronic conditions places a burden for contemporary health systems (1, 2). Multi-morbidity is associated with worse health outcomes, more complex clinical management, and increased health care costs (3). Several suggestions are available to take up the challenge by re-organizing the delivery of chronic illness care (4, 5). Based on these concepts, care management interventions have been developed and evaluated focusing on patients with multiple chronic conditions (6). Care management refers to ‘a set of activities designed to assist patients and their support systems in managing medical conditions and related psychosocial problems more effectively, with the aim of improving patients’ health status and reducing the need for medical services’ (7). These interventions share four core elements (8): (a) comprehensive assessment of patients’ medical and non-medical needs and resources, (b) implementation and monitoring of individualized, evidence-based care plans, (c) coordination of services between providers of medical and social care, and (d) enhancement of self-management capabilities among patients and caregivers.

In the context of type II diabetes, the concept of “self-care” (a synonym for self-management) plays an increasingly important role in preventing complications and coping with consequences of the condition (9). Relevant interrelated self-care dimensions for patients with type II diabetes include adaptations to diet, exercise, self-monitoring of blood glucose (SMBG), foot care, medication adherence and smoking (10). Diabetes typically occurs with or has other chronic diseases as consequences. Discordant comorbidities, such as depression (11), constitute an additional challenge for patients with diabetes to effectively conduct self-care activities.

Evidence suggests that, at least in the short run, self-care behaviors can be modified through self-management interventions (12). However, it is important that interventions aimed at supporting patients to cope with diabetes and potentially co-occurring conditions are person-centered (not disease-centered), comprehensive, embedded in the process of primary care within the health care system and take into account and mobilize community resources (13), especially in the context of socially disadvantaged populations (14). Isolated interventions, that use didactic teaching alone (14) or rely on technological, computer-based approaches alone (15) have been shown to be less (14) or not effective to improve cognitive, behavioral or emotional outcomes (15).

Although structured disease management programs (DMP) are embedded in routine primary care for patients with type II diabetes in Germany(16), their ‘disease-centered’ design does not sufficiently take into account the challenge of comorbidity. For care management programs, however, positive effects on quality of care and patients’ quality of life has been reported (7). But still, the effect of care management interventions on healthcare utilization and costs remains heterogeneous (7). This finding is reinforced by a recent systematic review of complex interventions designed to improve outcomes in patients with multi-morbidity (including comorbidity) in primary care and community settings (17). The

Dept. for General Practice and Health Services Research- University Hospital Heidelberg

„ A multi-center, individual-level randomized, 18-month, parallel-group superiority trial to compare the efficacy of a complex primary care practice network-based care management intervention versus usual care in the improvement of self-care behavior among patients with type II diabetes and multiple comorbidities (GEDIMApplus)“

Version 1.0 – 29.10.2013

review concludes that there is limited evidence on the care of patients with multi-morbidity, despite the prevalence of multi-morbidity and its impact on patients and healthcare systems. Included studies provided mixed results; partially due to the heterogeneity of included study populations as far as their chronic conditions are concerned. Research gaps were identified with respect to a paucity of economic analyses, the neglect of the impact of socioeconomic deprivation on multi-morbidity, and a small number of interventions with a clear definition of the ‘multi-morbid’ study population (17).

There are also specific research gaps related to care management among diabetes patients. Most interventions designed to improve the management of this population in primary care, outpatient or community settings have used biomedical surrogate parameters as primary outcome, and few have assessed the effects on patient reported outcomes (PROs) (13), such as self-care behavior, self-efficacy, attitudes, health service utilization, quality of life and/or psychological indicators (18). There are also few trials that report ‘patient-important’ outcomes related to death, morbidity (including hypoglycemic events) and quality of life. In a systematic review of 1057 ongoing and registered trials (in 2007), only 18% of trials reported such ‘patient-important’ outcomes (19).

The following features of interventions have been reported as promising to improve diabetes relevant outcomes (HbA1c, weight/BMI, lipids, blood pressure, health care utilization, physical activity), particularly among socially disadvantaged populations with diabetes (14): cultural tailoring, individualized assessment and reassessment, use of treatment algorithms by health care providers, focus on behavior-related tasks, use of feedback about patients’ control of disease or performance, and high intensity interventions (> 10 contact times) delivered over a long duration ( $\geq 6$  months).

Care management interventions in the German healthcare system have been evaluated with promising results for patients with osteoarthritis (20), depression (21), systolic heart failure (22), and index diseases such as diabetes mellitus, chronic obstructive lung disease, and chronic heart failure (6). However, further studies are necessary to explore the full potential of care management interventions to improve outpatient diabetes care in the context of multi-morbidity in Germany. Care management is particularly challenging to deliver for small primary care practices (PCPs). Practice-net based approaches might be a solution in this context, because they allow providing intensified care for patients from several practices, thus reducing the workload for smaller PCPs. These approaches in turn entail challenges regarding the flow of information between care managers, PCPs and other sectors in the delivery of relevant health care services according to individual need.

Based on an existing pilot project, we have developed a complex primary care practice-net (PCPnet) based, health-care-assistant (HCA) led, IT-supported care management intervention with integrated telephone-monitoring to improve diabetes care for patients with type II diabetes mellitus and multiple comorbidities. This study protocol documents the evaluation methods to be deployed during the ‘evaluation stage’ (23) of the complex intervention.

## 2. Study objectives

The primary objective of this study is to assess the efficacy of a PCPnet-based, HCA-led, IT-supported care management intervention with integrated telephone-monitoring for the improvement of self-care behavior among patients with type II diabetes mellitus and two or more comorbidities (see Chapter 8 and Figure 1 for a detailed description of the intervention).

### 2.1 Primary objective:

To determine, if there is a difference in the degree of change in diabetes related self-care behavior after 9 months (T1) of intensified care management (as add-on to usual care) compared to baseline (T0) between the intervention group (PTC) and the control group (TAU), which receives usual care only.

### 2.2 Secondary objectives

To assess:

1. if potential differences between both groups (PTC vs. TAU) in change of diabetes related self-care behavior compared to baseline (T0) can be sustained over an 18 months period (T2) with reduced intensity of care management and enhanced by self-monitoring of blood-glucose (whereas 'reduced intensity' refers to longer time-lags between telephone-monitoring contacts (Figure 1)).
2. if potential differences between both groups (PTC vs. TAU) in change of diabetes related self-care behavior after 9 months (T1)/18 months (T2) compared to baseline (T0) are confounded by patients' behavior at base-line and/or other important factors reported in the literature (sex, age, marital status/domestic partnerships, social status, migration status, type of comorbidity, perceived quality of health care, alcohol abuse and diabetes related emotional distress).
3. the changes for each dimension of diabetes related self-care behavior (diet, exercise, self-monitoring of blood glucose (SMBG), foot care, and smoking behavior) at T1/T2 compared to baseline (T0) between both groups (PTC vs. TAU).
4. if there are differences at T1/T2 between both groups (PTC vs. TAU) in change of glycosylated hemoglobin A1 (HbA1c %) compared to baseline (T0) among the subgroup of patients with a baseline value of HbA1c > 7.5 % (adjusted for the base-line value of HbA1c)
5. if there are differences at T1/T2 between both groups (PTC vs. TAU) in the cumulative incidence of (severe) symptomatic hypoglycemia among those patients at risk of this event during the respective observation period
6. if there are differences at T1/T2 between both groups (PTC vs. TAU) in change of health related quality of life (HRQL) and self-efficacy compared to baseline.

7. if the care management intervention is equitable in the distribution of potential health gains (self-care behavior, HbA1c% and HRQL) at T1.
8. differences between the intervention- and the control-group related to service utilization, direct and indirect costs of health care provision as well as the financial burden of informal care provided by patients' relatives at the end of observation time.
9. the cost-effectiveness of the primary endpoint (change in self-care behavior) and the secondary endpoint (HRQL) at end of observation time (if the intervention is efficacious).

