## Primary outcome

The intervention primarily aims at improving “self-care” as a multi-dimensional construct consisting of the five dimensions diet, exercise, self-monitoring of blood glucose (SMBG), foot care, and smoking behavior. This primary outcome is a patient reported outcome (PRO) and will be operationalized by the German version of the revised „Summary of diabetes self-care activities measure“ (10) (SDSCA). The English version of the revised SDSCA is a widely used, appropriate (24) valid and reliable tool with moderate test-retest-reliability (10) for capturing self-care behavior.

The German version (SDSCA-G) is based on a structured forward/backward translation of the original English instrument. The SDSCA-G will be deployed as part of paper-based questionnaire (see Appendix: Patientenfragebogen zur Erfassung der Selbstsorge) and consists of 11 items.

Scoring of items 1–10 (excluding smoking) uses days per week on a scale of 0–7 in which patients performed respective self-care tasks (24). For each group of items (e.g. diet) a mean number of days are calculated. The SDSCA scale is used as a continuous measure to determine if there are improvements compared to baseline at subsequent time points. As a result of strong ceiling effects, the ‘medication’ item is not included in the most recent recommended version [16].

No cut-off point has been determined to discriminate between adherence and non-adherence (24) and no minimal clinically relevant change in SDSCA ‘scores’ has yet been formulated (25). This means that, in order to determine a minimal clinically relevant change for this study, the research team needs to draw upon (i) published data on the degree of change in SDSCA values reported in interventions designed to improve self-management, and (ii) estimates about ‘realistic’ changes that the intervention can bring about.

The primary outcome used to assess the efficacy of the intervention is the difference in mean change in SDSCA-G ‘score’ of items 1-10 (excluding smoking) per patient compared to baseline (T0) after 9 months of intervention (T1) between both groups (PTC vs. TAU) determined on the basis of patients’ self-reports.

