The equity-efficacy ratio (45) (and respective 95 % confidence intervals) will be calculated as the ratio of effects at T1 on health outcomes (change in SDSCA score; HbA1c%; HRQL) between the highest and the lowest socioeconomic group (related education/income/subjective social status) for both groups (PTC vs. TAU) compared to To. Additional consideration of social group sizes will be ensured by calculating the concentration index (PTC vs TAU) and plotting concentration curves at To and T1 respectively.

Subgroup analysis for nominal social groups will be performed by means of interaction terms for migration status (Turkish migrants, non-Turkish migrants, participants without migration background) to be included in the regression equations for respective health outcomes (change in SDSCA score; HbA1c%; HRQL) at T. If the tests of subgroup interaction effects are significant below the 0.05 level, further analysis will be performed to check whether their effects are independent (46).

Statistical analyses related to secondary outcomes 8 and 9 (see pages 4-5) focus on the incremental cost effectiveness ratio (ICER) (47, 48). The ICER relates cost differential to outcome differential between intervention and control groups. Bootstrap methods model statistical uncertainty and the net-benefit approach is applied (49, 50). Maximum willingness to pay thresholds and cost-acceptability curves (51, 52) will be determined. Sensitivity analyses will provide information on robustness of assumptions.

Because no adjustments for multiple endpoints are planned, findings (especially those related to secondary outcomes and subgroup analyses(46)) will be interpreted with caution in view of the number of statistical tests undertaken. Only the result of the primary efficacy analysis will be interpreted in a confirmatory manner. Confirmatory subgroup analyses are not planned. No interim analysis with regard to efficacy will be done.

In case of missing data, multiple imputation will be used to complete the data set for analysis. A complete-case analysis will be performed to assess the influence of missing data and the value of adopting multiple imputation methods.

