## **11.4 Sample size calculation**

Sample size was calculated based on the expected difference between the two treatment groups in mean change in the SDSCA-G score from baseline (T0) compared to 9 months after baseline (T1). Based on data from published studies, which used the revised SDSCA as outcome measure (53-55) we estimated a mean change of 0.5 days (standard deviation 2.0) in the overall SDSCA-G “score” (calculated as the sum of days of items 1 - 10 divided by 10) per patient in 9 months as minimal clinically relevant change.

Based on these estimates, a total of 506 patients (253 per arm) would be required to detect an effect size (Cohen’s d) of 0.25 between-groups (PTC vs. TAU) (50% relative increase in self-care) with a power of 80 % applying a two-sided t-test for two independent samples at a significance level of 5%.

Assuming a drop-out rate of 15% over the period of 9 months, the overall required sample size amounts to a total of 582 participants (291 per arm).

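### Objective 9 makes the cost-effectiveness analysis conditional on an undefined efficacy result; the Summary and section 11.2 plan it with no stated condition

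*Protocol*

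**What the plan says.** Section 2.2, objective 9, covers cost-effectiveness for self-care behaviour and for health-related quality of life (HRQL), to be assessed "at end of observation time (if the intervention is efficacious". Nothing in the protocol says what would count as efficacious for this purpose.

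The Summary (Analysis) has no such condition: "To relate cost differential to outcome differential between intervention and control group the incremental cost effectiveness ratio will be calculated".

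Section 11.2 opens its economic paragraph with "Statistical analyses related to secondary outcomes 8 and 9 (see pages 4-5) focus on the incremental cost effectiveness ratio (ICER") and continues "The ICER relates cost differential to outcome differential between intervention and control groups". It then adds "Bootstrap methods model statistical uncertainty and the net-benefit approach is applied" and "Maximum willingness to pay thresholds and cost-acceptability curves (51, 52) will be determined". It does not state a condition either. The list of secondary outcomes stops at 8, so the 9 cited there can only be objective 9.

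The nearest thing to a definition of efficacy is in the Primary outcome section: "The primary outcome used to assess the efficacy of the intervention is the difference in mean change in SDSCA-G" after 9 months (T1). Objective 9 concerns the end of observation, which is 18 months (T2).

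**The concern.** Three places describe the same analysis and one of them makes its existence depend on a result. The trigger could be a significant difference in SDSCA-G at T1, a difference of at least the 0.5 days that section 11.4 calls minimally relevant, an effect at T2, or an effect on HRQL. Whether an ICER exists would then be settled after the results are known. This is more than detail for an analysis plan, because the objective itself decides whether there is an analysis.

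The condition also fits poorly with the planned methods. Bootstrap, net benefit and acceptability curves describe joint uncertainty in cost and effect, and none of them needs a significant effect. Service use and costs, SDSCA-G and EQ-5D are collected to T2 in any case. An intervention with an uncertain effect may save money or may cost much for little gain, and a decision maker needs to know which. The Introduction names the shortage of economic analyses as a research gap, and this rule would leave the trial silent on it after a null result.

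Finally, if an ICER is reported only after a favourable effect estimate, the effects in reported ICERs are on average too large.

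**Working it through.** **Inputs.** From section 11.4: difference 0.5 days, SD 2.0, power 80%, 253 per arm (506 in total), "applying a two-sided t-test for two independent samples at a significance level of 5"%, drop-out 15%, 582 recruited. From section 7: allocation 1:1. Assumptions of this check, not in the protocol: the condition means a significant benefit on SDSCA-G at T1; the T1–T2 correlation of the estimated effects is 0.3 to 0.9; the true effect is the same at T1 and T2.

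**The plan's own figure.** A two-sample t-test with d = 0.5/2.0 = 0.25 needs 252.13 per arm, so 253 and 506 in total. This agrees with section 11.4. Applying 15% drop-out to the 582 recruited leaves 582 × 0.85 = 494.7, or about 247 per arm. Results are given for 253 and 247.

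**Formulas.** SE = 2.0 × √(2/n). Significance limit c = 1.96 × SE. For a true effect δ, let a = (c − δ)/SE. Then
- P(ICER reported) = 1 − Φ(a)
- mean effect given significance = δ + SE × φ(a)/(1 − Φ(a))

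**Worked case, n = 253, δ = 0.5.** SE = 2.0 × √(2/253) = 0.178 and c = 0.349 days. a = (0.349 − 0.5)/0.178 = −0.85. P(reported) = 0.803. Mean effect given significance = 0.5 + 0.178 × 0.2775/0.803 = 0.561 days, which is 12% too large.

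| True T1 effect | n per arm | ICER reported | No ICER | Mean T1 effect if significant | Excess |
|---|---|---|---|---|---|
| 0.50 | 253 | 80% | 20% | 0.561 | 12% |
| 0.50 | 247 | 79% | 21% | 0.565 | 13% |
| 0.40 | 253 | 61% | 39% | 0.511 | 28% |
| 0.40 | 247 | 60% | 40% | 0.515 | 29% |
| 0.25 | 253 | 29% | 71% | 0.460 | 84% |
| 0.25 | 247 | 28% | 72% | 0.465 | 86% |

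**From T1 to T2.** With equal standard errors, the excess at T2 is the correlation times the excess at T1.
- δ = 0.5: from 0.3 × 12.3% = 4% to 0.9 × 12.9% = 12%.
- δ = 0.25: from 0.3 × 84% = 25% to 0.9 × 86% = 77%.

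**The ratio itself.** Simulating cost divided by the T1 effect, with constant cost and 253 per arm, the median reported ICER is 0.92 times the true value at 0.5 days and 0.57 times at 0.25 days.

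**HRQL.** The same argument applies through the correlation between the EQ-5D and SDSCA-G effect estimates. The protocol does not give it. If it is zero, there is no excess.

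**The case against.** **Section 11.2 may inherit the condition.** It cites item 9, and item 9 carries the condition. On that reading only the Summary is out of line, and a summary may drop a qualifier. This stands as an arguable reading, so the conflict is softer than two plainly opposed rules. It does not define the trigger, and it does not explain why methods that need no significant effect should wait for one.

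**The consequences are limited.** A reader might infer that a non-significant trial would report no cost or quality-of-life evidence at all. The protocol does not support that. Objective 8 (service use, costs, burden of informal care) and objective 6 (HRQL and self-efficacy) carry no condition, and the Secondary outcomes section plans the cost analysis outright. Only the step that joins cost and effect is at risk.

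**The number itself does not change.** A reader might also infer that an ICER computed under the condition is wrongly calculated. It is not: the figure from a given trial is the same with or without the condition. The rule changes which trials report one. It is prespecified and visible, and section 11.2 treats only the primary analysis as confirmatory. All of this stands and is why the point is minor.

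**The T1 percentages are not the ICER error.** Objective 9 is assessed at T2, so the T1 excess cannot be read across directly. The T2 figures rest on an assumed correlation. This also stands.

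**Conclusion.** The point holds as a wording inconsistency with an undefined trigger, and it is minor. Applied as written, objective 9 would withhold the joint cost-effectiveness and cost-utility result when efficacy is not shown. It would also select reported ICERs towards favourable values.

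If the condition is p<0.05 for benefit at T1, with SD 2.0 and about 250 per arm, the chance of no ICER is about 20% at the design effect. The T1 effect given significance is 12–13% too large at a true 0.5 days and 84–86% too large at 0.25 days. At T2, with the assumed correlation of 0.3 to 0.9 and an unchanged true effect, the excess is about 4–12% and 25–77%. For HRQL it may be zero. The bias is therefore modest if the design assumption is right and large only if the true effect is well below it. Another definition of efficacious would give other figures. The primary efficacy conclusion does not depend on any of this.

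**What to change.** Delete the parenthetical efficacy condition from objective 9. In the Summary, objective 9 and section 11.2, state in the same terms that the ICER, net benefit and acceptability curves will be computed and reported on all randomised patients whatever the primary result.

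The cost is one deleted clause and one aligned sentence. No patient, visit, instrument or sample-size change is needed. The only extra work is running an analysis that is already planned if the primary test is not significant.
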